## Abstract

**Background:**

German statutory health insurances are pursuing the goal of improving treatment of chronically ill people by promoting networks of health care providers and supporting treatments that reflect the current medical knowledge. The so-called PNP program is a collaborative care program developed by a German statutory health insurance, which defines specific rules on psychiatric, neurological, psychosomatic, and psychotherapeutic treatment. It aims to strengthen provision of guideline-based outpatient treatment and collaboration between different health care providers. It includes the general practitioners’ program, which aims to strengthen the coordinating role of GPs. This study aims to evaluate the PNP program.

**Methods:**

To evaluate the effectiveness of the PNP program, we will conduct a prospective non-randomized controlled trial with primary data comparing patients enrolled in the PNP program and in the general practitioner program (intervention group) to patients enrolled only in the general practitioner program and patients who receive usual care (control groups). To evaluate costs and level of detail of diagnoses in care of patients with PNP program, we will use routinely collected secondary administrative health data in a retrospective quasi-experimental design. Patients who are at least 18 years old, insured by the statutory health insurance AOK, and on sick leave due to one of the mental or neurological diagnoses (affective, anxiety, somatoform or adjustment disorders, alcohol use disorders, schizophrenia, multiple sclerosis) will be included. We will collect data at baseline and at 12-months follow-up. Health-related quality of life (primary data) and direct costs (secondary data) caused by outpatient and inpatient service utilization and medication will be the primary outcomes. We will analyze data using (generalized) linear mixed models and exploratory analyses. We will use entropy balancing to control for possible differences between the groups. We will use an exploratory sequential design including qualitative and descriptive statistical analyses to assess the structure and process quality of the PNP program among health care providers.

**Discussion:**

The results will help to develop a comprehensive picture of collaborative care programs for mental and neurological health care from the perspective of patients, health care providers, and health insurance companies.

**Trial registration:**

German Clinical Trial Register DRKS00013114

**Electronic supplementary material:**

The online version of this article (10.1186/s12888-018-1914-5) contains supplementary material, which is available to authorized users.

## Background

Mental and neurological disorders are common and severe health threats, so they play a decisive role in health care [1, 2]. It is estimated that about 27% of the adult EU population, is or has been affected by at least one mental disorder in the past 12 months [3]. Mental disorders are related to a high degree of personal suffering, disease burden, and health impairment [1, 4]. Several mental disorders, such as depression, alcohol use disorders, bipolar disorders, schizophrenia, and panic disorders, are among the 20 leading causes of disability [2]. Multiple sclerosis, one of the most relevant neurological disorders, is related to impairment of functioning and quality of life [5]. Consequently, mental and neurological disorders represent a major challenge for the health care system and produce high direct as well as indirect costs [6, 7].

The German health care system consists of different health care sectors: primary and specialist care in the outpatient setting, and inpatient care. Statutory or private health insurances cover health care costs; whereby 90% are covered by statutory health insurances. For treatment of mental and neurological disorders, patients can seek GPs, specialist outpatient care from psychiatrists, neurologists, psychotherapists, specialists in psychosomatic medicine as well as inpatient care in neurologic, psychiatric, or psychosomatic hospitals. Although a well-developed mental health care system exists, there is still need for improvement regarding early and correct detection of mental illnesses in primary care and regarding the reduction of intersectoral barriers. For example, GPs can generally identify only about half of the patients with depression and can accurately exclude four of five non-depressed individuals [8]. In addition, there are large delays between detection and adequate treatment of mental disorders [9, 10]. Consequently, patients are on greater risk to maintain high degrees of burden [11–13], lose their motivation to seek treatment or seek treatments that are not sufficiently evidence-based. Even at treatment initiation, speration of the responsibilities of health care providers in differenct sectors impede changing health care sectors (e.g. primary care, specialist care, and inpatient care) [12]. This fragmented mental health care system is a major weakness in Germany [14]. Consequently, overcoming those intersectoral barriers by developing innovative care networks may optimize care of patients with mental and neurological disorders.

To organize patient-centered care, integrated care models may be useful. Clinical practice guidelines recommend stepped and collaborative care models for the treatment of depressive [15] and anxiety disorders [16]. Stepped care aims to tailor evidence-based interventions to patients’ needs, starting with the lowest intensity [17]. In case of non-response, patients receive the next higher level of treatment intensity. Collaborative care aims to strengthen cooperation between different health care providers in order to provide evidence-based and comprehensive treatment.

Studies indicate that stepped and collaborative care models are effective and improve outcomes (e.g. adherence, reduction of depressive symptoms) compared to treatment as usual among patients with depression [18]. A meta-analysis calculated small to medium effect sizes for the effectiveness of collaborative care (depression, mental and physical quality of life, social role function) compared to usual care or with less integrated models (e.g. patient education, consultation-liaison services) among patients with mental disorders [19]. The results of two meta-analyses provide evidence for the effectiveness of collaborative care models compared to care as usual in reducing symptoms among patients with anxiety disorders (standard mean difference = 0.35 95% CI 0.14–0.56) [20] and depression (standard mean difference = 0.34 95% CI 0.25–0.43) [21]. In addition, collaborative care models improve adherence, quality of life, and satisfaction with care among patients with depression [21]. Among patients with multiple scleroses, a long term observational study without control groups did not find effects on disability and health related quality of life [22].

Cost-effectiveness studies showed that the collaborative care models lead either to decreased costs or to slightly increased costs, whereas quality of health care was considerably improved. Although, costs for outpatient care usually increase through collaborative care models, costs for inpatient care decrease [6, 23]. For instance, collaborative care models lead to savings in costs after 2 years among patients with depression [24] and lead to a reduction of acute inpatient treatments among patients with multiple sclerosis [22]. Due to a decrease in days of incapacity to work, indirect costs are reduced among patients with depression [25]. Thus, collaborative care models demonstrate a favorable cost-benefit ratio among patients with mental disorders [26]. However, there is a lack of evidence for the effectiveness of collaborative care programs for patients with multiple sclerosis.

In contrast to other countries, the majority of health care costs in Germany arise from inpatient treatment. To address problems with the fragmented mental health care system in Germany, selective care contracts between particular statutory health insurance companies and health care providers can be concluded in accordance with the German Social Security Code V [27]. These selective care contracts regulate parts of the primary and outpatient care beyond standard care (which is regulated in the collective contract) among people with statutory health insurance. Statutory health insurance companies are committed to provide insurees opportunies for certain selective care contracts (contracts regarding general practitioners-centered care). Health care providers and patients can participate voluntarily in selective care models.

Two selective care programs developed and implemented by the German statutory health insurance AOK Baden Wuerttemberg (AOK BW) are the “general practitioners program” (“HausarztProgramm”) and the “specialist program” (“FacharztProgramm”). Insurees enrolled in the “specialist program” can receive care in the so-called PNP program, if they need care in the fields of psychiatry, neurology, psychosomatics and psychotherapy. The PNP program aims to strengthen collaboration between different health care providers and provision of individualized, guideline-based and biopsychosocial outpatient treatment. Therefore, correct and detailed diagnoses are needed. Differences between components of interventions compared to usual care are described in Table 1. The AOK BW comprehensively implemented the PNP program in Baden-Wuerttemberg (Southwest Germany) and 590,000 patients are receiving care within the specialist program (February 2018). This program needs to be evaluated.

**Table 1 Tab1:** Differences between components of interventions

	Usual care	General practitioners program	PNP program
Requirements for participation (patients)	- free choice of health care providers with a license in Baden-Wuerttemberg	- minimum time of participation: 12 months - commitment to seek help from GPs enrolled in the program only - commitment to seek help from GPs first (exception: emergencies, gynecologist, ophthalmologists, pediatricians)	- enrolled in the general practitioners program and the specialist program - minimum time of participation: 12 months - commitment to seek help from health care providers enrolled in the program only - commitment to seek help from GPs first (exception: emergencies, gynecologist, ophthalmologists, pediatricians)
Requirements for participation (health care providers)	- license in Baden-Wuerttemberg	- license in Baden-Wuerttemberg - GP	- license in Baden-Wuerttemberg - psychotherapists and specialists in psychiatry, neurology, psychotherapy, or psychosomatic medicine - enrolment in at least one of three modules: psychiatry, neurology, psychotherapy
Role of GPs	- diagnosis, treatment, referral to specialists	- diagnosis, treatment, referral to specialists - guiding through care: structured coordinating and communication to specialists care and merging results of medical examinations	- diagnosis, treatment, referral to specialists - guiding through care: structured coordinating and communication to specialists care and merging results of medical examinations
All providers			
Compensation and diagnoses	- health care services for patients with specific and unspecific diagnoses in accordance with ICD-10 are billable	- health care services for patients with specific and unspecific diagnoses in accordance with ICD-10 are billable - fee for cooperation with specialists	- health care services for patients with predominantly specific diagnoses in accordance with ICD-10 are billable (e.g., for depressive disorders, only the specific codes F32.0-F32.3, F33.0-F33.4 are billable; the unspecific codes F32.8, F32.9, F33.8, and F33.9 are not billable) - fee for cooperation with specialists and GPs
Social service	- social service of the AOK Baden Wuerttemberg	- more structured cooperation between health care provider and social service of the AOK Baden Wuerttemberg	- more structured cooperation between health care provider and social service of the AOK Baden Wuerttemberg
Quality management	- mandatory continuous training courses	- mandatory continuous training courses - participation in quality circles on drug therapy (once per quarter) for GPs	- mandatory continuous training courses - participation in quality circles on drug therapy (once per quarter) for GPs (optional for specialists)
Psychotherapy			
Differences in compensation	- higher payment of regular sessions compared to preparatory sessions (2–4 preparatory sessions)	- higher payment of regular sessions compared to preparatory sessions (2–4 preparatory sessions)	- higher payment for first sessions (acute / initial care = 10/20 sessions) compared to long-term therapy and compared to usual care - higher payment for group psychotherapy compared to usual care - collective incentives for saving sickness benefits
Organization	- review process for approval of long-term psychotherapy	- review process for approval of long-term psychotherapy	- no review process for approval of long-term psychotherapy
Treatment content	- Cognitive Behavioral Therapy - Psychodynamic Psychotherapy - Psychoanalytic therapy - Neuropsychological therapy - Hypnosis - Eye Movement Desensitization and Reprocessing (EMDR)	- Cognitive Behavioral Therapy - Psychodynamic Psychotherapy - Psychoanalytic therapy - Neuropsychological therapy - Hypnosis - Eye Movement Desensitization and Reprocessing (EMDR)	- Cognitive Behavioral Therapy - Psychodynamic Psychotherapy - Psychoanalytic therapy - Additional treatment methods depending on diagnosis: ○ Neuropsychological therapy ○ Hypnosis ○ Eye Movement Desensitization and Reprocessing (EMDR) ○ Systemic psychotherapy ○ Biofeedback ○ Interpersonal therapy
Additional guidelines on accessibility	/	/	- for acute cases: initial session within 3 days; start of psychotherapy within 7 days after established diagnosis - for initial treatment: start of psychotherapy within 4 weeks after established diagnosis
Psychiatry			
Additional compensation	/	/	- additional supplements for → counselling (e.g. supportive counselling for patients with depression) → provision of technical equipment → prescription of discounted medication → collective incentives for the prevention of hospital admissions
Additional guidelines on accessibility	/	/	- limit of waiting time up to 30 min - for acute cases: first doctor’s appointment within the same day
Neurology			
Additional compensation	/	/	- additional supplements for → counselling (e.g. Multiple Sclerosis counselling: 6 units of 20 min per year) → provision of assistants (e.g. with special training on Multiple Sclerosis care)
Additional guidelines on accessibility	/	/	- limit of waiting time up to 30 min - for acute cases: first doctor’s appointment within the same day

In summary, international evidence shows that collaborative care models leads to long-term improvement in patient reported outcomes as well as to reduced costs among patients with mental disorders. To evaluate the benefit of collaborative care models, effects of these models need to be assessed from different perspectives considering various outcome parameters. Nonetheless, multi-perspective and comprehensive evaluations of collaborative care models, like the PNP program implemented in Germany, are currently lacking. Hence, the purpose of this study is to evaluate the PNP program.

## Methods

### Study aims

This study will evaluate the PNP program with regard to (i) effectiveness (patient reported outcomes), (ii) direct and indirect costs, (iii) the level of detail of diagnoses, and (iv) structure and process quality. The study focuses on the health care of patients with the most common mental disorders and the relevant neurological disorder multiple sclerosis.

We will take the perspectives of patients, health care providers, and cost units into account by using patient-related primary and secondary data as well as primary data from health care providers. To evaluate the (i) effectiveness, (ii) costs, and (iii) the level of detail of diagnoses in care with PNP program, we will compare the intervention group, which consists of patients receiving care within the PNP program (intervention group: IG-PNP) with patients, who participate in the “general practitioners program”, but not the PNP program (control group: CG-GP) and with patients, who receive usual care (control group: CG-UC) (Table 1). To evaluate the (iv) structural and process quality of the PNP program, we will survey health care providers enrolled in the PNP program.

### Research questions, hypotheses and study design

#### Effectiveness

*Is treatment within the PNP program more effective compared to the treatment in the control groups (CG-GP, CG-UC) with regard to health related quality of life among patients with mental or neurological disorders (main research question)?*

i.1.) We expect higher scores of health-related quality of life for the IG-PNP compared to the control group CG-GP and to the control group CG-UC.

i.2.) We expect higher scores of functional health, lower illness-specific symptom burden as well as higher patient satisfaction for the IG-PNP compared to CG-GP as well as CG-UC.

*Which groups of patients benefit most from the PNP program?*

i.3.) We expect patients with chronic and severe focus diagnoses to benefit most from the PNP program. Accordingly, we expect chronicity (illness duration) and degree of severity to be significant moderators of the interaction effect. We will investigate additional moderators like gender, age, educational status, diagnoses and comorbidity.

We will conduct a prospective non-randomized controlled trial among patients to answer research questions related to effectiveness. We will include consecutively recruited patients belonging to the three groups (IG-PNP, CG-GP, CG-UC). We will measure health-related quality of life, patient-relevant symptom severity and satisfaction with care at baseline (t_0_, date of sick leave) and at 12-month follow-up (t_1_). Although randomized controlled trials could provide the best evidence in evaluation studies [28], we cannot randomize participants to the three groups for ethical and contractual reasons. In order to prevent the selection bias, we will recruit participants for all three groups in the same area in Germany (Baden Wuerttemberg). We will use entropy balancing to control for potential differences between intervention and control groups. No independent data monitoring committee to determine if the study should be modified or discontinued is necessary, because patients receive interventions irrespective of study continuation or participation. We will monitor and document study responses and discuss possible adaptions if necessary.

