### Sample size calculation

The sample size was calculated for being able to detect a clinically relevant effect regarding the primary outcome health-related quality of life (SF-36) between IG-PNP and control groups CG-GP and CG-UC. Meta-analyses [19, 21, 32] calculated small to moderate effect sizes for collaborative care models. According to Cohen, a small to moderate effect size is defined as d = 0.30 [33]. Given an expected correlation of *r* = 0.4 between outcome at baseline and at follow-up, we will need *n* = 441 patients (*n* = 147 per group) to detect this effect with α = 0.05, power of 0.80 and without the random effect of health care providers offices [34]. Given an expected intraclass correlation of *p* = 0.10 and 100 health care providers in each group, we multiplied the necessary sample size with the design effect of DEF = 1.047 (1 + (147/100–1)*0.10) in consideration of random effects. Consequently, we need to include *n* = 153 patients per group (460 patients in total) in the analyses. We plan to overrecruit by 16.5% to compensate losses of statistical power through possibly different group sizes (IG- PNP ≈ 27%, CG-GP ≈ 22%, CG-UC ≈ 51%) with an allocation ratio of 2.33. Accordingly, we aim to include 536 patients in the analyses. Based on experiences, we expect a response rate of 7% for baseline. We expect dropout rates 40% for follow-up assessments. Consequently, we plan to contact *n* = 12,800 patients to receive data from *n* = 538 patients. We will perform dropout analyses for both study dropout and intervention dropout.

For analyzing direct and indirect costs (ii) and level of detail of diagnoses (iii), we will use complete secondary data from all patients meeting the inclusion criteria in 2015. Because of the exploratory approach, we did not conduct a formal sample size calculation for the evaluation of structure and process quality (iv).

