#### Effectiveness

We will use mixed linear models with fixed effects of group membership (IG-PNP / CG-GP / CG-UC) and further covariates, if necessary (e.g., in case of substantial inbalance between groups) to test the hypotheses regarding effectiveness. Primary medical practice affiliation will be modelled via random effects to adjust for possible clustering. Moderator analyses will be performed by adding interaction terms to the model. Results with *p* < .05 will be considered statistically significant.

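### Hypothesis i.3 expects two significant moderators, but the unadjusted p < .05 rule also covers an open list of at least five more, in a sample sized only for the main group difference

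*Protocol article*

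**What the plan says.** All references are to the protocol article.

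- **Research questions, hypotheses and study design, Effectiveness.** Which patients benefit most is a separate research question. Its hypothesis, i.3, expects chronic and severe cases to gain most and continues: "we expect chronicity (illness duration) and degree of severity to be significant moderators of the interaction effect". The next sentence opens the list: "We will investigate additional moderators like gender, age, educational status, diagnoses and comorbidity". Hypothesis i.1 sets two comparators: "We expect higher scores of health-related quality of life for the IG-PNP compared to the control group CG-GP and to the control group CG-UC".
- **Statistical analysis, Effectiveness.** The method and the decision rule stand in consecutive sentences: "Moderator analyses will be performed by adding interaction terms to the model. Results with *p* < .05 will be considered statistically significant". The rule makes no exception and does not distinguish the two expected moderators from the others.
- **Sample size calculation.** The target is the difference between groups on the SF-36, where "a small to moderate effect size is defined as d = 0.30". No interaction enters the calculation.
- **Use of the label exploratory.** The article attaches it to the provider evaluation (Structural and process quality) and to the analysis of diagnosis detail (Statistical analysis, Level of detail of diagnoses). It does not attach it to any moderator analysis.

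**The concern.** A rule that calls every interaction with p < .05 significant treats a moderator predicted in advance and one picked from an open list as the same kind of evidence. With at least seven moderators and two control groups, the chance that something crosses the threshold is well above 5% even if the programme works equally well for everyone.

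The opposite error matters too. The sample was sized for the average group difference, so a real difference in benefit between subgroups may easily be missed. A reader could then take a non-significant chronicity or severity interaction as evidence against i.3. Both errors bear on the stated question of who benefits most.

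**Working it through.** **Inputs from the article.** d = 0.30, baseline to follow-up correlation 0.4, α = 0.05, power 0.80, design effect 1.047, 536 patients analysed, split 27/22/51% (all from Sample size calculation); two expected moderators, five further named ones and two control groups (from the effectiveness hypotheses).

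**Assumptions made here.** Binary moderators, no loss of precision from the entropy-balancing weights, one outcome only, and diagnoses counted as a single moderator. Weighting loss would lower power. More outcomes, or separate contrasts among the eight disorders, would raise the number of tests.

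**1. The plan's own figure.** With baseline adjustment the variance factor is 1 − 0.4² = 0.84.

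n per group = 2 × (1.960 + 0.842)² × 0.84 / 0.30² = 146.5, so 147.

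This reproduces the stated 147 per group and confirms that the target is a two-group main effect.

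**2. False positives when no moderation exists.** The article does not say whether the interaction is tested jointly over the groups or separately against each control, so both are shown.

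| Family | Calculation | At least one p < .05 |
|---|---|---|
| 7 moderators, one joint test each, uncorrelated | 1 − 0.95⁷ | 30% |
| 7 × 2 = 14 separate tests, independent | 1 − 0.95¹⁴ | 51% |
| 14 tests, shared PNP arm, moderators uncorrelated | simulation | 48% |
| 14 tests, shared arm, moderators correlated 0.3 | simulation | 44% |
| 14 tests, shared arm, moderators correlated 0.5 | simulation | 38% |
| 2 expected moderators, one joint test each | 1 − 0.95² | 9.75% |
| 2 × 2 = 4 separate tests, shared arm | simulation | 16–17% |
| 4 separate tests, independent | 1 − 0.95⁴ | 18.5% |

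The planned arms are 0.27 × 536 = 144.7 (PNP), 0.22 × 536 = 117.9 (GP) and 0.51 × 536 = 273.4 (usual care). Sharing the PNP arm gives the two contrasts a correlation of (1/144.7) / √[(1/144.7 + 1/117.9)(1/144.7 + 1/273.4)] = 0.54, which the simulations use.

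**3. Power for one interaction.** For a 50/50 moderator each arm is halved, which multiplies the variance of the contrast by four:

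SE = √[4 × 0.84 × 1.047 × (1/n_PNP + 1/n_control)]

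- Against GP: SE = √(3.518 × 0.01539) = 0.233. For 0.30 SD, 0.30/0.233 − 1.96 = −0.67, so power is 25%.
- Against usual care: SE = √(3.518 × 0.01057) = 0.193. For 0.30 SD, 0.30/0.193 − 1.96 = −0.40, so power is 34%.
- Equal groups with an effective 147 per arm: 29%.

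| Assumed interaction, 50/50 split | vs GP | vs usual care |
|---|---|---|
| 0.15 SD | 9% | 12% |
| 0.30 SD | 25% | 34% |
| 0.45 SD | 49% | 65% |
| 0.60 SD | 73% | 88% |

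With a 25/75 split, the 0.30 SD row falls to 20% and 27%. With equal groups, 80% power needs a difference of about 0.60 SD between subgroups, twice the effect planned for the whole group.

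**The case against.** Several points on the other side are sound.

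- **The article is a condensed account.** An analysis plan may exist, and test form and multiplicity usually belong there. The lack of an adjustment method is therefore not the finding. What remains is that the article does state a rule, and as worded that rule reaches the open list.
- **Moderation is visibly subordinate.** The article names a main research question and one primary outcome for the patient survey, and it separates expected from additional moderators. A reader might infer a confirmatory claim on seven or more moderators, but the text does not support that. Only two are predicted, the others are merely to be investigated, and the word confirmatory is not used. Numbering does not settle the matter either: hypothesis iii.a is numbered and phrased as an expectation, yet is analysed descriptively.
- **i.3 is directional.** An interaction with gender or education could not confirm it. That limits the damage to i.3 itself, but not to the broader question of who benefits most.
- **The error rate depends on the decision rule.** If a moderator had to be significant against both controls in the same direction, the chance of any false positive would be about 7% for seven moderators and 2% for two. The article sets no such requirement for moderators.
- **Sizing for the main effect is normal.** The article claims neither interaction power nor family-wise error control, so low power is not in itself a mistake.

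A second tempting reading is that a significant moderator would be about as likely false as true. This cannot be derived. The 30–51% is the chance of any false positive when no moderator is real. The share of findings that are false also depends on how many moderators are real and how strong they are, and the article gives neither. If both expected moderators are real and uncorrelated, the chance of detecting at least one in four separate tests runs from 32% at 0.15 SD to 99% at 0.60 SD.

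**Conclusion.** The point holds as a limited one. The stated p < .05 rule does not separate two predicted moderators from an open list of at least five, and it is applied in a sample sized only for the main effect. Under no moderation, at least one significant result arises with probability of about 30% (seven uncorrelated joint tests, lower if correlated) or 38–51% (fourteen pairwise tests). For the two predicted moderators the figure is about 10–19%. Power per test is about 25–34% for a 0.30 SD interaction with a 50/50 split. The rates rest on one outcome, and the power figures on binary moderators and no precision lost to weighting. Severity is low: the main comparison on quality of life is unaffected, and the problem is how moderator results may be described.

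**What to change.** In Statistical analysis, Effectiveness:

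1. Limit the p < .05 rule for moderation to chronicity and severity, with one joint group-by-moderator test each. Under no moderation, the chance of any false claim is then at most 9.75% if the two tests are independent. Holm across the two would bring it to at most 5%, at some loss of power. Whether to add it is a matter of preference.
2. Label gender, age, education, diagnoses, comorbidity and any further moderators exploratory. Report their interaction estimates with 95% confidence intervals and make no significance claim.
3. State that the sample size does not cover interactions, so a non-significant moderator is not evidence that moderation is absent.

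This changes wording only and needs no further patients or data. The cost is that the additional moderators can no longer be declared statistically significant.
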